## Methods

This protocol is informed by the TREND Statement Checklist^45^ for reporting non-randomised interventions and the SPIRIT guidelines^46^ for reporting clinical trial protocols.

### Design

The study has an uncontrolled, within-group, with a pre-post and 3-month follow-up design with embedded mixed-method process evaluation. All participants will receive a guided internet-administered self-help programme lasting 12 weeks. Potential participants will be identified via the Swedish Childhood Cancer Registry (the National Quality Registry, initiated in 1982).

### Eligibility criteria

Eligible participants will be aged 15–25 years at study start; have been diagnosed with cancer when aged 13–18 years; have been treated at a paediatric oncology unit in Gothenburg, Lund, Linköping or Umeå in Sweden; have completed successful cancer treatment (according to the paediatric oncology unit if the person is 15–17 years at study start or according to self-report if the person is ≥18 years at study start); be able to read and write text in Swedish; have access to email, the internet and a mobile telephone, and report a need for psychological support. Little data are available to guide the selection of screening measures for this population.^47^
^48^ As such, no cut-off scores on screening measures will be used to determine inclusion into the study; however, the feasibility of screening procedures will be examined to inform the procedures for a future controlled trial.

Potential participants will be excluded if they currently receive psychotherapy or if they display symptoms of severe depression, active suicidality, psychosis, bipolar disorder and/or alcohol and/or substance abuse in immediate need of treatment (based on a clinical assessment combining information from the 9-item Patient Health Questionnaire (PHQ-9)^49^ and the Mini-International Neuropsychiatric Interview (MINI.)^50^). People excluded on this basis will be guided to appropriate healthcare.

### Sample size

Recent reports recommend sample sizes of 50–60 participants^51^
^52^ to assess feasibility outcomes and estimate sample size for a definitive trial. However, since the target population in Sweden is very small, coupled with experiences from other successful feasibility studies^53–55^ and recommendations,^56^ we aim to include at least 30 participants in the present study.

### Recruitment, setting and procedure

The names and addresses of potential participants will be identified via the Swedish Childhood Cancer Registry. Internet search engines will be used to identify telephone numbers for those aged ≥18 years. For those aged 15–17 years, telephone numbers will be retrieved from the paediatric oncology units. Invitations to participate will be issued in two stages. First, people whose telephone numbers have been identified will be contacted via telephone, in alphabetical order, by study personnel and will receive brief information about the study. Second, if fewer than 30 people have been included when all people with identified telephone numbers have been contacted, written information about the study will be sent to people whose telephone numbers have not been identified or who have not been reached via telephone. Information will be posted on social media via patient organisations, for example, the Swedish Childhood Cancer Foundation and UngCancer (a non-profit organisation supporting adolescents and young adults affected by cancer in Sweden), to raise awareness about the study.

### Informed consent and eligibility interview

People who have been contacted via telephone or post and who are interested in participating will be directed to a secure website where they can register, provide informed consent and answer questions regarding symptoms of depression (PHQ-9^49^) and Generalized Anxiety Disorder 7-item scale (GAD-7^57^). Written information about the study will be sent to caregivers of people aged 15–17 years who have registered on the website.

Potential participants will thereafter be contacted via telephone by a clinical psychologist for an eligibility interview to confirm inclusion criteria, that is, completed successful cancer treatment; able to read and write text in Swedish; have access to email, the internet and a mobile telephone; and not currently receiving psychotherapy. The psychologist will also provide a description of the programme, its aims and the types of problems addressed. Potential participants will be asked about their own situation and whether they experience any of the problems addressed in the programme. They will thereafter decide themselves whether they have a need for the support provided, with young adults considered experts of their own perceived needs. Potential participants meeting the inclusion criteria and perceiving a need for psychological support will be interviewed with the MINI^50^ to identify people with psychiatric problems in need of immediate treatment or further examination. People reporting such problems are excluded and guided to appropriate healthcare services. If a potential participant reports suicide ideation but the risk of suicide is assessed as low, the person is offered participation and a safety plan is set up collaboratively. People meeting the eligibility criteria will be offered the opportunity to participate. If the person is aged 15–17 years, an assessment of whether he/she understands what participation implies will be performed to determine whether his/her consent to participate is sufficient or if it needs to be complemented with caregiver consent. If the person appears not to understand the implication of participation, he/she will be asked for permission for study personnel to collect informed consent from his/her caregiver(s). If the caregiver(s) does(do) not consent, participation will not be continued. The flow of participants through the study is shown in figure 1.

**Figure 1 BMJOPEN2016013906F1:**
[figure not shown]
CONSORT diagram. GAD-7, Generalized Anxiety Disorder 7-item scale; MINI, Mini-International Neuropsychiatric Interview; PHQ-9, 9-item Patient Health Questionnaire.

### Self-help programme

#### Development

Development of the programme was informed by the UK Medical Research Council (MRC) guidelines for developing and evaluating complex interventions.^44^ Research identifying the specific psychological problems and needs experienced by young people diagnosed with cancer during adolescence^30–38^ and evidence-based cognitive–behavioural models for treating anxiety and depression^58–66^ guided development of the programme. Moreover, development included consultations with paediatric oncology nurses and mental health staff, psychologists with extensive experience of working with CBT with adolescent and young adult mental health populations, psychologists with experience of developing CBT interventions for chronic illness populations, representatives of patient organisations and researchers with experience of developing and evaluating internet-based CBT interventions. Communication agencies were consulted to edit the layout of the material and the secure internet portal—the U-CARE-portal (‘the Portal’)—via which the programme will be delivered. Teachers with extensive experience of educating adolescents reviewed a portion of the text material with regard to readability. Importantly, a group of adolescents and young adults with and without lived experience of cancer during adolescence, formed for the purpose of the present project (n=10), were consulted to review programme content, layout, readability of text material and the procedures planned to test the programme. Additional adolescents and young adults with and without experience of cancer were consulted during development for input on programme content, layout, readability of text material and procedures planned to evaluate the programme.

#### Content

Based on descriptions of self-help^22^ and taxonomies of level of support,^24^ the present programme can be described as guided internet-administered self-help and includes provision of self-help material via the Portal, an initial support session via telephone in which individual problem analyses and idiographic goals are formulated, and regular guidance from a therapist via telephone and the Portal to follow participants' progress and processes.

The programme will be available via the Portal and consists of ICBT, psychoeducation and interactive peer support. The ICBT is considered the core of the programme and is organised into six chapters: introduction, depressive symptoms, anxiety and worry, post-traumatic stress, body dissatisfaction and wrapping up, with the first and last chapters being mandatory. The remaining chapters are each divided into five parts and are assigned to participants based on their needs. Participant needs are determined by individual problem analyses combining baseline questionnaires and interview outcomes, a clinical assessment and a collaborative discussion concerning specific areas and goals the participant would like to prioritise. The clinical assessment follows the Five Areas Assessment Model,^67^ based on the CBT model, providing structure to the assessment.^68^ The chapter(s) best matching participants' problem analyses will be chosen, with additional chapters added later based on participant need and preference. Participants will be encouraged to work with one part of a chapter per week. Each part consists of text material describing treatment components, homework assignments and questionnaires in which homework is reported to the therapist, with text material available as PDF and MP3 files. The majority of the chapters include a PowerPoint presentation, which serves to clarify important treatment principles and help participants make connections between the material and their own lives. Extensive efforts have been made to include ‘common factors’ in the programme and material.^69^ To develop and maintain a therapeutic alliance,^69^ the programme has been developed to engage participants in the text material by including statements of empathy, genuineness and warmth, narratives referring to struggle and recovery, examples to help participants relate the text material to their own lives and personal metaphors for emotional distress.^70^ Online supplementary appendix 1 presents an overview of the ICBT chapters and homework assignments and key references used to develop the ICBT content.

10.1136/bmjopen-2016-013906.supp1supplementary appendix

#### Guidance from therapists

Participants will work independently with the programme over 12 weeks and receive weekly and at-need guidance from a therapist via messages within the Portal or by telephone. How participants would prefer to be guided is decided collaboratively at study start. Therapists will provide feedback on homework, reinforce progress, validate difficulties and encourage and guide continued work with the ICBT following a standardised treatment manual. Participants will be able to contact their therapist via the Portal or telephone for additional guidance, which will be received within one working day. Given the explorative nature of the study, no maximum time limit for guidance sessions has been set. Participants who do not log in or show low activity in the ICBT will be contacted via text message and/or telephone. During the first week of access to the programme, participants will be contacted via telephone by a therapist for an individually tailored individual problem analysis and formulation of idiographic treatment goals (approximately a 30 min session). On the basis of this analysis, participants will be recommended the ICBT chapters that best match their problems.

#### Optional support functions

Participants will have access to a number of optional support functions built into the ICBT programme, including a library, interaction with other participants and a Questions and Answers (Q&A) function. The library consists of written texts, also available as MP3 files, about common problems and concerns related to cancer during adolescence, alongside video interviews with people with lived experience of cancer during adolescence. Further, the programme provides the possibility to interact with other participants via a chat room, a discussion forum, a private one-to-one messages function and a diary function. Interactions are monitored by study personnel to detect potential risk to self or inappropriate communication, with participants fully informed on study entry and when accessing the chat room for the first time. If risk of suicide/self-harm is detected, standard safety procedures according to the ethical approval will be followed. Participants will also be able to pose questions via a Q&A function, receiving an answer from a study therapist within one working day. Finally, weekly group chat sessions with a study therapist will be offered. Each additional support function is optional and participants do not receive recommendations regarding optimal level of engagement with these additional support functions.

#### Participant adherence

Number of logins, opened ICBT items and completed homework assignments are continuously logged and used to assess participants' adherence to the ICBT. Number of chat sessions, forum posts, private messages, diary posts, questions in the Q&A function and visits to the chat room, forum, diary, library and Q&A functions are logged to examine feasibility and acceptability of optional support functions.

#### Therapist training and adherence

Before study-start, all therapists will take part in a one-day workshop on the programme by the first author (MA), who was part of the programme development team. Therapists will receive weekly group clinical supervision focusing on case discussions, skills development and at-need supervision by a licensed psychologist with experience of working with young people and CBT. Written communication between participants and therapists will be logged and continuously reviewed by the clinical supervisor to assess therapists' adherence to the ICBT protocol and competence in delivering the ICBT. A 15% sample of the communication between therapists and participants within the programme will be reviewed for therapists' adherence to the ICBT protocol and competence in delivering the ICBT according to an adherence measure developed for the YoungCan programme. Findings will be used to identify areas in the programme and therapists training that require modification and/or further development.

### Outcome measurements

#### Feasibility outcomes

The feasibility outcomes concern methodological, procedural and clinical uncertainties^42–44^ related to recruitment and eligibility criteria, data collection, attrition, resources needed to complete the study and programme, safety procedures and process evaluation including participants' and therapists' adherence to the programme, participants' acceptability of the programme and of the study methodology, and exploration of mechanisms of impact. A summary of feasibility outcomes is provided in table 1. In addition, progression criteria, where applicable, which will be used to determine whether revisions should be considered before proceeding to a controlled trial,^43^ are presented.

**Table 1 BMJOPEN2016013906TB1:** Feasibility outcomes and progression criteria

Outcome	Evaluation	Progression criteria to controlled trial*
Recruitment and eligibility	Number of people identified via the Swedish Childhood Cancer Registry, invited via telephone, invited via letter, assessed for eligibility	No criteria set
	Percentages of people interested in participation, assessed for eligibility, meeting the inclusion criteria and included, of the total number identified	≥15% interested in participating of the total number identified≥10% included of the total number identified
	Ambiguities regarding eligibility criteria	No criteria set
	Numbers scoring above/under recommended cut-offs on clinical outcome measures	No criteria set
	Reasons for ineligibility	No criteria set
	Reasons for non-participation	No criteria set
Data collection	Percentage of participants completing assessments	70% answering all questions at all assessments
	Numbers of missing items relating to clinical, psychological and health economics outcomes	No criteria set
	Types and number of potential uncertainties in diagnostic interviews	No criteria set
Attrition	Rates of dropout from study and programme	No criteria set
Resources needed to complete the study and the programme	Length of time for: Participants to work through the programme Participants to complete questionnaires and interviews Therapists to deliver the programme Study personnel to administer the study	No criteria set
Safety procedures	Ambiguities regarding standard safety procedures Types and numbers of measures undertaken to assure patient safety Types and numbers of unforeseen safety issues	No criteria set
Participants’ adherence to the ICBT and use of optional support functions	Number of: Logins Opened ICBT items, completed homework assignments Chat sessions, forum posts, private messages, diary posts, questions in the Q&A function Visits to the chat room, forum, library and Q&A functions	70% completing the introduction ICBT chapter, and the first two parts of an individually assigned chapter
Therapists’ adherence to programme	Content of online written therapist-participant communication	No criteria set
Participants’ acceptability of programme and data collection and exploration of mechanisms of impact	Reasons for poor attendance and withdrawal from study and programme	No criteria set
	Impressions and experiences of working with the programme (including positive and negative consequences) and of completing questionnaires and interviews	70% of participants using the programme reporting that it is helpful <1 participant reporting substantial negative consequences related to participation in the study and/or programme

*If one or more criteria are not met, revisions should be considered before proceeding to a controlled trial.

ICBT, internet-based cognitive–behavioural therapy; Q&A, Question and Answer function.

#### Psychological and health economics outcomes

The feasibility of using a number of psychological and health economics measurements will be examined to assess whether or not to include them in a controlled study. The PHQ-9^49^ will be used to measure symptoms of depression and the GAD-7^57^ to measure anxiety symptoms. Body dissatisfaction will be measured with the Body Image Scale (BIS)^71^ and post-traumatic stress symptoms using the Posttraumatic Stress Disorder Checklist—Civilian version (PCL-C).^72^ Reactions to social interaction situations will be measured with the Social Interaction Anxiety Scale (SIAS).^73^ The EuroQol EQ-5D^74^ will be used to calculate quality-adjusted life years. Aspects regarding use of healthcare services, employment, absence and sick leave will be examined with a modified short version of the Trimbos and Institute of Medical Technology Assessment Cost Questionnaire for Psychiatry (TiC-P),^75^ assessing direct and indirect medical costs and indirect non-medical costs.

#### Demographics and clinical variables

Data on age, gender, diagnosis and date of first diagnosis will be collected via the Swedish Childhood Cancer Registry. Self-reported information on education, employment status (including studying), ethnicity, relationship status, family situation, housing situation, cancer recurrence including date, date of end of treatment, type of treatment, presence and type of late effects and potential receipt of psychological treatment before and after diagnosis will be collected at baseline.

### Data collection

Psychological and health economics-related self-reported data will be collected at the eligibility interview, the baseline assessment and the assessments 3 and 6 months after the baseline assessment. Data will be collected either via telephone or online via the Portal. Prompts will be sent via text message and reminders will be sent via text message or provided by telephone. The outcome measures and mode of administration, at each assessment, are shown in table 2.

**Table 2 BMJOPEN2016013906TB2:** Outcome measures at each assessment

Measure	Eligibility interview	Baseline assessment	Assessment at 3 months postbaseline	Assessment at 6 months postbaseline	Mode of administration
Demographics and clinical variables		x			Online
PHQ-9	x		x	x	Online
GAD-7	x		x	x	Online
BIS		x	x	x	Online
PCL-C		x	x	x	Online
SIAS		x	x	x	Online
EQ-5D		x	x	x	Online
Modified TiC-P		x	x	x	Online
MINI		x	x	x	Telephone

BIS, Body Image Scale; EQ-5D, EuroQol 5-dimension questionnaire; GAD-7, Generalized Anxiety Disorder 7-item scale; MINI, Mini-International Neuropsychiatric Interview; PHQ-9, 9-item Patient Health Questionnaire; PCL-C, Posttraumatic Stress Disorder Checklist-Civilian version; SIAS, Social Interaction Anxiety Scale; TiC-P, Trimbos and Institute of Medical Technology Assessment Cost Questionnaire for Psychiatry.

Data collection via telephone at 3 and 6 months post baseline will be performed by psychologists and clinical psychology students not otherwise involved in the study. Potential participants/participants who report psychiatric symptoms in need of treatment or further psychiatric examination will be guided to appropriate healthcare and if the person is aged 15–17 years, their caregiver(s) will be informed.

### Process evaluation

To assess the programme's relevance in terms of participants' acceptability of and adherence to the programme, and to generate hypotheses regarding mechanisms of impact, semistructured interviews will be conducted via telephone at baseline and 3 months postbaseline. At baseline, participants will be asked to describe problems, hypotheses about problem development and maintaining factors, experiences of psychological treatment and expectations of the programme. Three months after baseline, participants will be interviewed regarding impressions and experiences of working with the programme and of completing questionnaires and interviews. Moreover, participants' activity in the Portal will be logged continuously to assess adherence to the ICBT and the feasibility and acceptability of optional support functions. Non-attendees, that is, those included but who do not attend the first week telephone session or complete the ICBT introduction chapter and poor attendees, that is, those included who attend the first week telephone assessment and complete the ICBT introduction chapter but fail to complete more than the first part of the assigned ICBT chapter, will be asked about their reasons for not adhering to the programme and what a programme should include. To explore non-acceptability of the programme and methods, participants who choose to exit the study will be asked if they agree to be interviewed about their reasons for exiting and what a programme should include. Interviews will be conducted via telephone by clinical psychology students not involved in delivering the programme and are anticipated to last ∼45 min. If the participant permits, the interview will be digitally recorded. Participants will be given the option to complete the interview over one or two telephone sessions.

### Data analyses

Data analyses will primarily be descriptive and will address the primary outcomes relating to the feasibility of the programme and study methods.

#### Quantitative analyses

The CONSORT diagram will be used to illustrate participant flow. Numbers of potential participants identified via the Swedish Childhood Cancer Registry, invited via telephone, invited via letter, assessed for eligibility, eligible and included will be reported. The percentages of potential participants willing to undergo eligibility assessment of the total number invited, of potential participants overall meeting the eligibility criteria out of the total number invited and of participants overall enrolled in the study out of the total number invited will be calculated with exact 95% CIs. Reasons for ineligibility, ambiguities regarding eligibility criteria, reasons for non-participation and numbers included via telephone versus postal letter will be reported. To generate hypotheses regarding appropriate screening measures, numbers scoring above/under cut-offs recommended for similar populations on clinical outcome measures related to problems addressed in the ICBT will be reported.

Follow-up rates and numbers of missing items relating to clinical outcomes will be calculated with 95% CIs alongside means and SDs for the number of reminders via text message and telephone. Potential assessment uncertainties in diagnostic interviews will be reported alongside means and SDs for time taken to complete questionnaires and interviews. Descriptive statistics including the means and SDs or medians and IQRs and change scores for each outcome measurement at the eligibility interview, baseline and 3 and 6 months postbaseline will be reported. Attrition proportions (both programme and study dropout) will be reported with 95% CIs.

Means, SDs and frequencies for each Portal activity relating to adherence to the ICBT including logins; opened ICBT items and completed homework assignments will be reported; alongside means, SDs and frequencies for each Portal activity relating to the use of optional support functions including chat sessions; forum posts; private messages; diary posts; questions in the Q&A function; visits to the chat room, forum, diary and Q&A functions, and visits to the library will be reported. Means, SDs and frequencies of participant–therapist contact within the Portal and via telephone will be reported and therapist adherence measures will be summarised with means and SDs and collated in total and by therapist.

Means and SDs for the length of time taken for participants to work through the programme; for participants to complete the eligibility assessment, baseline, follow-up assessments and interviews; for therapists to deliver the programme; for therapist training and supervision, and for project personnel to administer the data collection procedures from the invitation to the 3-month follow-up, will be reported to estimate the required resources and to assess the feasibility of the programme and suggested methods. Finally, potential ambiguities regarding standard safety procedures, types and numbers of measures undertaken to assure patient safety and types and numbers of unforeseen safety issues will be reported.

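### Counts above and under cut-offs, with no group named and no split by reported need, show at most the share of people with need whom a cut-off would miss, not whether it separates need from no need

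*Protocol article*

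**What the plan says.** The Eligibility criteria section requires that participants "report a need for psychological support". It states that "no cut-off scores on screening measures will be used to determine inclusion into the study" and that "the feasibility of screening procedures will be examined to inform the procedures for a future controlled trial".

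The Informed consent and eligibility interview section gives the order of events. Interested people go to a website where "they can register, provide informed consent and answer questions regarding symptoms of depression" (PHQ-9) and anxiety (GAD-7). A psychologist then telephones, describes the programme and asks about the person's situation: "They will thereafter decide themselves whether they have a need for the support provided". The MINI follows only for those who meet the inclusion criteria and perceive a need.

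Table 2 places PHQ-9 and GAD-7 at the eligibility stage, and BIS, PCL-C and SIAS first at baseline.

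The planned analysis is in Quantitative analyses: "To generate hypotheses regarding appropriate screening measures, numbers scoring above/under cut-offs recommended for similar populations on clinical outcome measures" related to the problems addressed in the programme will be reported. Table 1 lists the same item under recruitment and eligibility as "Numbers scoring above/under recommended cut-offs on clinical outcome measures", with no progression criterion. Neither place says who is counted, and neither splits the counts by reported need.

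**The concern.** The plan gives this analysis a purpose, which is to suggest suitable screening measures for the controlled trial. A screening cut-off has two properties: how many people with need it keeps, and how many people without need it removes. A one-way count can speak to the first, and only when everyone counted has a need. It cannot speak to the second.

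The controlled trial's screening choice could therefore rest on half of the relevant table, although data for part of the other half will already be held. A cut-off that flags many people with need looks good on these counts even if it flags people without need just as often.

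**Working it through.** The document gives no calculation for this analysis, so there is no figure to reproduce. The check concerns what the counts can identify.

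**Inputs.** At least 30 included (Sample size). At least 15% interested and at least 10% included, of those identified (Table 1). Need is required for inclusion (Eligibility criteria). PHQ-9 and GAD-7 are answered before need is decided (Informed consent and eligibility interview). The shares above and under cut-offs used below are illustrations; the document gives none.

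**Exact interval.** For x of n, the Clopper-Pearson 95% limits are the 2.5% quantile of Beta(x, n − x + 1) and the 97.5% quantile of Beta(x + 1, n − x).

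**1. Counts in included participants.** All 30 have reported a need, so the expected number above a cut-off is 30 × sensitivity. Specificity does not enter.
- Sensitivity 0.6, specificity 0.9: 30 × 0.6 = 18 above; Youden index 0.6 + 0.9 − 1 = 0.5.
- Sensitivity 0.6, specificity 0.4: again 18 above; Youden index 0.6 + 0.4 − 1 = 0.

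Both give 18/30 = 60% (40.6 to 77.3%). The output is the same for a cut-off that discriminates and one that does not.

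**2. What those counts do give.** They estimate how many people with need a cut-off would miss.
- 12/30 above (40%, 22.7 to 59.4%): 18 missed.
- 24/30 above (80%, 61.4 to 92.3%): 6 missed.

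This is usable, sensitivity-type information, and it allows measures to be compared on that one property.

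**3. A pooled count over everyone assessed.** Take 30 people with need and, as an assumption, 15 without.
- Cut-off A: 18/30 with need above, 3/15 without need above. Pooled 21/45. Youden index 18/30 + 12/15 − 1 = 0.4.
- Cut-off B: 14/30 with need above, 7/15 without need above. Pooled 21/45. Youden index 14/30 + 8/15 − 1 = 0.

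The pooled counts are identical, so naming a wider group without splitting by need does not solve the problem.

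**4. How large the group without need could be.** At the Table 1 thresholds, 30 included at 10% means 30 / 0.10 = 300 identified; 15% interested is 45; 45 − 30 = 15 interested people are not included, for any reason. Some of these will be on current psychotherapy, excluded on clinical grounds, or lost before the call. Treating all 15 as having no need is therefore an assumption. Over a range of 5 to 15, with 80% under the cut-off as an illustration:
- 4/5: 28.4 to 99.5%
- 8/10: 44.4 to 97.5%
- 12/15: 51.9 to 95.7%

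Splitting by need makes the missing half estimable, but imprecisely.

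**The case against.** A reader might infer that the planned counts can say nothing about which measure to choose. The documents do not support that. Step 2 shows that they can argue against a cut-off that misses many people with need, and the stated aim is only to generate hypotheses within a mainly descriptive analysis. This part of the objection stands.

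A reader might also infer that the plan restricts the PHQ-9 and GAD-7 counts to included participants and so discards the comparison group. The text does not say so. No denominator is named, and Table 1 places the item under recruitment and eligibility. The restriction is certain only for BIS, PCL-C and SIAS, which start at baseline. The point survives because a pooled count does not show discrimination either (step 3).

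Reported need is an imperfect reference. It is decided after the programme has been described, as need for the support on offer, by people already interested enough to register. It is known only for those who reach that step of the call, not for every registrant. These limits stand and must be stated with the table.

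Finally, denominators and cross-tabulations are often left to a statistical analysis plan, which is not shown here, and an unseen plan may already contain the split. But the article itself states both the method and its purpose, and the method as stated answers only part of that purpose.

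**Conclusion.** The point holds in a limited form. The stated analysis yields, at best, the share of people with self-reported need whom each cut-off would miss. It cannot show whether a cut-off separates people with need from people without it, whether the count covers the included or everyone assessed.

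The data needed for an exploratory look at separation will exist for PHQ-9 and GAD-7 only. The achievable gain is modest: with an assumed 5 to 15 people without need, the interval around an illustrative 80% under the cut-off has a lower limit between 28% and 52%. That is enough to raise or question a hypothesis about a measure, not to settle one. The conclusion rests on self-reported need as the reference and on the assumed size of the group without need. The case for acting is the low cost, not a threat to the study's main feasibility results.

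**What to change.** In Quantitative analyses, and in the matching row of Table 1, name the group counted and add the split by need:

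- For all registrants who reach the need decision in the eligibility call, report PHQ-9 and GAD-7 above and under each cut-off by self-reported need (yes/no), with exact 95% CIs, labelled exploratory.
- Keep in the table people with need who are later excluded on clinical grounds. The PHQ-9 feeds that exclusion, so dropping them would cut off the upper end of its scores.
- For the same reason, do not compute PHQ-9 accuracy against the clinical exclusion decision: the measure would be judged against a decision it helped to make.
- State that need is judged against the support this programme offers.
- State that BIS, PCL-C and SIAS give only the proportion above the cut-off in people with need.

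The cost is one table from data already collected, with the yes/no answer on need recorded for everyone who reaches that step. The downside is that the group without need is self-selected and probably small, so intervals will be wide and the table must not be presented as validation of a screening measure.
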